### Analysis

#### Analysis of Quantitative Data at the Patient Level

Descriptive statistics will be used to describe the characteristics of the users and nonusers for each group of participants. To assess whether nonusing and using responders are representative of polypharmacy patients, parents of young children, and other patients in the 3 practices, we will compare their characteristics with those of the population they were obtained from using two sample *t* tests for continuous variables and chi-square tests for categorical variables. We will perform multiple linear regression analyses to investigate the effects of age, sex, education level, perceived health, health literacy, and internet and eHealth use on the adoption of the PHR and access to the summary record, defined as having logged in at least once to the PHR and the summary record. We will use descriptive analyses for data derived from the questionnaires about perceived usefulness, experiences, opinions, and concerns and for log in data on the number of days (hit days) the users have accessed their GP records and viewed different parts of the records during the study period. For each group of patients, we will compare the means changes in in-person levels of playing an active role in decision making and in the management of condition and medication adherence over the 6-month study period between users and nonusers using two sample *t* tests. Similarly, we will analyze the secondary outcomes. We will use a *P* value <0.05 (two sided) as a criterion for statistical significance for all analyses. Because of the explorative character of our study, we will not correct for multiple testing using a more stringent *P* level. We will deal with the problem regarding multiple testing in the interpretation of results by primarily focusing on the primary outcomes and by integrating the qualitative findings with the results of quantitative comparisons. SPSS Statistics software (IBM Corp, Armonk, NY, United States) will be used for the analyses.

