### Setting, Study Population, and Sample Size

The study will be conducted in 3 group practices of GPs in the southeast of the Netherlands, where 18 GPs provide primary care to approximately 22,000 patients. This setting is a pragmatic choice based on the health information system that is used in these practices and the willingness of the GPs to provide Web-based access to their records and to participate in this study. Assuming that uptake, use, and effects will differ among different groups of patients, we will recruit a random sample from three groups of patients: (1) adult patients using five or more different types of medication (polypharmacy patients), (2) parents of children aged <4 years, and (3) other adult patients (those who do not belong to the first two groups). Both polypharmacy patients and parents of young children are frequent users of GP services, with an expected number of 5 and 2 contacts, respectively, with the GP during the 6-month study period [39]. They are likely to differ in terms of health status, age, internet use, and computer skills. Patients aged >75 years and those with severe cognitive or psychiatric problems will be excluded; furthermore, patients for whom access to the records may be harmful to themselves or others according to the GPs will be excluded.

Because of the lack of available figures, a proper power analysis to determine the sample size is not feasible. However, we expect that a sample of 50 users and 100 nonusers of the PHR in each group will be suitable for our aims. We assume that the uptake of the intervention will be approximately 10%, based on experiences in these practices along with the adoption rates of other eHealth interventions and based on the adoption rates of these services in the Netherlands [16]. With an expected participation rate of 25%-50% for research using questionnaires in general practice in the Netherlands [40,41] and an assumed uptake of the intervention of approximately 10% and taking into account that GPs may exclude some patients, we will use a random sample of 550 patients for each group for the quantitative study: 550 polypharmacy patients, 550 parents of children aged <4 years, and 550 other patients.

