#### Routine Patient Data From General Practices

To describe our sample of study participants in relation to the population that the sample was obtained from, we will collect routine data (age, sex, prevalence of chronic disease, and frequency and number of contacts with the GP or practice nurse) from GP practices for the groups of patients from which we have obtained our samples.

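### The representativeness check applies two-sample tests to responders and a source group that, as written, contains them, so it rejects too rarely; a minor error in a secondary check

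*Protocol article*

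**What the plan says.** The purpose is stated in the Protocol article, Analysis of Quantitative Data at the Patient Level: "To assess whether nonusing and using responders are representative of polypharmacy patients, parents of young children, and other patients in the 3 practices". The method follows in the same sentence: "we will compare their characteristics with those of the population they were obtained from using two sample" *t* tests for continuous characteristics and chi-square tests for categorical ones.

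The comparator is described under Routine Patient Data From General Practices. Age, sex, chronic disease and contact data are to be taken "from GP practices for the groups of patients from which we have obtained our samples". Neither section says that sampled patients or responders are taken out of these groups first.

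The analysis section also sets a *P* "value <0.05 (two sided) as a criterion for statistical significance for all analyses", which covers this check.

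**The concern.** A two-sample *t* test and a chi-square test both treat the two sets of data as independent. Here every responder is also a member of the comparator. The responder mean and the group mean are positively correlated, so their difference varies less than the two-sample formula supposes. The computed standard error is too large, the test statistic too small, and a real difference between responders and their source group is missed more often than the nominal level implies.

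That is the unhelpful direction for this check. The article expects 25% to 50% participation, so self-selection is a real possibility, and this is the only formal comparison of responders with their own practice groups that it describes. A nonsignificant result is likely to be read as reassurance.

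**Working it through.** The article gives no standard error, power or detectable difference for this check, so there is no figure of its own to reproduce. The question is how far the planned test departs from its nominal level.

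**Inputs from the Protocol article**
- Setting, Study Population, and Sample Size: "we will use a random sample of 550 patients for each group for the quantitative study", and "With an expected participation rate of 25%-50% for research using questionnaires in general practice". Responders per group: 550 × 0.25 ≈ 138 to 550 × 0.50 = 275.
- Same section: the target per group is 50 users and 100 nonusers, 150 in all.
- Same section: the three practices are places "where 18 GPs provide primary care to approximately 22,000 patients". The sizes of the three patient groups are not given.
- Level: 0.05, two-sided.

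**Assumption:** group size N is shown over 600 to 15,000, because the documents do not fix it.

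**Standard error.** Let n responders lie inside a group of N, f = n/N, with common standard deviation s. Let r be the responder mean and q the mean of the rest.
1. The group mean is f·r + (1−f)·q, so responders minus group equals (1−f)(r − q).
2. Var(r − q) = s²[1/n + 1/(N−n)] = s²/[n(1−f)].
3. The true variance of responders minus group is therefore (1−f)² × s²/[n(1−f)] = s²(1−f)/n = s²(1/n − 1/N).
4. The planned test uses s²(1/n + 1/N) = s²(1+f)/n.
5. Ratio of planned to true standard error: sqrt((1+f)/(1−f)).
6. True two-sided size: 2[1 − Φ(1.96 × ratio)].

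Example, n = 150 and N = 1,000: f = 0.15; ratio = sqrt(1.15/0.85) = 1.163; size = 2[1 − Φ(2.280)] = 0.023.

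| n | N (assumed) | f | SE ratio | True size at nominal 5% |
|---|---|---|---|---|
| 150 | 600 | 0.250 | 1.29 | 1.1% |
| 150 | 1,000 | 0.150 | 1.16 | 2.3% |
| 150 | 2,000 | 0.075 | 1.08 | 3.5% |
| 150 | 15,000 | 0.010 | 1.01 | 4.8% |
| 275 | 1,000 | 0.275 | 1.33 | 0.9% |
| 275 | 2,000 | 0.138 | 1.15 | 2.4% |
| 50 (users) | 1,000 | 0.050 | 1.05 | 3.9% |

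Simulation (8,000 runs per setting) agrees. For n = 150, N = 1,000 the rejection rate is 0.021 (Student), 0.022 (Welch) and 0.022 (chi-square). For n = 275, N = 1,000 it is 0.009, 0.009 and 0.010.

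**Power.** Let d be the responder-minus-rest difference in SD units.
- Planned test: Φ{[(1−f)d − 1.96·sqrt(1/n + 1/N)] / sqrt((1−f)/n)}.
- Responders against the rest: Φ{d/sqrt(1/n + 1/(N−n)) − 1.96}.

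For d = 0.2, n = 150, N = 1,000:
- planned: (0.170 − 0.1716)/0.0753 = −0.02, power 49%;
- corrected: 0.2/0.0886 − 1.96 = 0.30, power 62%.

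The same formulas give, planned to corrected:
- n = 275, N = 1,000: 59% to 81%
- n = 150, N = 2,000: 60% to 65%
- n = 150, N = 15,000: 67.6% to 68.3%
- n = 50, N = 1,000: 25% to 28%

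**Equal variances.** If responders are clearly more variable than the group, the pooled Student test can err the other way: simulated size is 0.08 at an SD ratio of 1.3 with n = 150, N = 2,000. Welch stays conservative there, at 0.033.

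**The case against.** The case against giving this much weight is strong on size.

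- **f cannot be fixed.** Everything depends on it, and only a total of about 22,000 patients is stated. A reader might infer a particular sampling fraction for parents from a guessed number of young children on the list. The documents support no such figure, and the sampled group is parents, not children. This stands; only a range can be shown.
- **The difference is not also diluted.** A reader might think that having responders inside the comparator shrinks the difference as a second, separate bias. It does not. The difference and its true standard error both shrink by (1−f), so the whole loss is the single factor above. Responders minus group is also a sensible measure of representativeness.
- **n may be smaller.** Users and nonusers may be compared with the group separately. For 50 users the effect is small.
- **The check is descriptive.** No inclusion rule, weighting or outcome comparison depends on it, and no pass rule is set. The study is called explorative, and Strengths and Limitations already says that the practices are not representative of Dutch general practice. This stands, and limits the point to a minor one.
- **A condensed article may leave out detail.** The full protocol might remove responders from the comparator. But the article names both the tests and the comparator, and as written they overlap. This is a stated method that does not fit the data, not an omission.

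**Conclusion.** The point holds as a minor error. As written, the samples overlap, and with similar variances (or with Welch's test) the planned tests reject too rarely. For 150 responders the true size runs from about 1.1% to 4.8% as the assumed group size goes from 600 to 15,000. The effect may matter for the parent or polypharmacy group if either is small, roughly 600 to 2,000. It is negligible for the other adults and small for users taken alone.

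A reader might go further and conclude that unrepresentative samples will generally be accepted, or that the study's effect estimates are compromised. The documents support neither. The comparison of users with nonusers uses different data contrasts and is untouched, and for large groups the departure from 5% is trivial.

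**What to change.** Reword the representativeness analysis so that responders are compared with the remainder of the same source group, that is, the group minus the responders, wherever the same routine variables can be obtained for both. In simulation this returns the *t* test to a size of 0.049 to 0.053. Where the remainder cannot be formed, compare responders with the group value in a one-sample comparison, using the finite-population standard error s·sqrt((1−f)/n). For n = 150, N = 1,000 that is 0.075s, against 0.088s in the planned test. State the group sizes.

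In either case give the difference with its confidence interval. A nonsignificant result does not show representativeness even after the correction: with 50 users in a group of 1,000, power for a 0.2 SD difference is only about 28%.

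The change is to analysis wording, with no new recruitment. The small downside is that the subtraction needs responders to be identifiable in the routine data. The article does not say that these data are individual-level or linked. The baseline questionnaire asks about contacts in the last 3 months, whereas no window is given for the routine contact data, so the self-reported counts cannot simply stand in for routine ones.

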**Methods:**

We will conduct a multilevel mixed-methods study in which the PHR and Web-based access to the summary record will be offered for 6 months to a random sample of 500 polypharmacy patients, 500 parents of children aged <4 years, and 500 adults who do not belong to the former two groups. At the patient level, a controlled before-after study will be conducted using surveys, and concurrently, qualitative data will be collected from focus group discussions, think-aloud observations, and semistructured interviews. At the general practice staff (GP staff) level, focus group discussions will be conducted at baseline and Q-methodology inquiries at the end of the study period. The primary outcomes at the patient level are barriers and facilitators for using the PHR and summary records and changes in taking an active role in decision making and care management and medication adherence. Outcomes at the GP staff level are attitudes before and opinions after the implementation of the intervention. Patient characteristics and changes in outcomes related to patient involvement during the study period will be compared between the users and nonusers of the intervention using chi-square tests and t tests. A thematic content analysis of the qualitative data will be performed, and the results will be used to interpret quantitative findings.

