### Outcomes of Interest

The primary outcomes of interest are the predictors for adoption of the PHR, which are defined as using the PHR at least once to access the summary of the GP record, including patient characteristics and perceived barriers and facilitators. Other primary outcomes are those related to patient involvement: playing an active in role decision making, disease management, and medication adherence. We included medication adherence because this is related to the knowledge about the condition and treatment and shared decision making and may be facilitated by having an overview of the medication list [42,43].

The secondary outcomes are patient-reported changes in use of GP services (number and type of contacts), patients’ confidence in their communication with the GP, knowledge about the disease, satisfaction with GP care, and patient-reported perception of changes in the doctor-patient relationship. Patient-reported benefits and drawbacks and the opinions of the GP staff about patients using the PHR and access to the summary of the GP record are also secondary outcomes. We do not expect health outcomes to improve during the 6-month study period; therefore, we will not assess these.

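### Adoption, a yes/no primary outcome, is assigned multiple linear regression, whose standard errors are unreliable for uneven predictors that truly relate to adoption

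*Protocol article*

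**What the plan says.** The article's section on quantitative analysis at the patient level states: "We will perform multiple linear regression analyses to investigate the effects of age, sex, education level", followed by perceived health, health literacy, and internet and eHealth use. The dependent variable is adoption, "defined as having logged in at least once to the PHR and the summary record". That is one login or more against none.

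The Outcomes of Interest section uses the same dichotomy and puts this analysis first: "The primary outcomes of interest are the predictors for adoption of the PHR, which are defined as using the PHR at least once". Study Design separates users from nonusers in the same way. Hit days, the only count of use, are assigned to descriptive analysis, so the linear model cannot be meant for them. The article mentions neither robust standard errors nor a deliberate linear probability model.

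On expected adoption, the sample-size section says "We assume that the uptake of the intervention will be approximately 10" per cent and "we expect that a sample of 50 users and 100 nonusers of the PHR in each group will be suitable for our aims".

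**The concern.** Ordinary linear regression takes the residual variance to be the same for everyone. For a 0/1 outcome the variance is p(1-p), so it changes whenever a predictor changes the probability of adoption. The planned model therefore misstates the precision of the associations it is meant to find. It can also return fitted probabilities below zero.

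This matters because the article handles multiple testing by giving most weight to the primary outcomes, with two-sided P<0.05 as the criterion, and this is the only multivariable model it describes for the quantitative data. Some planned predictors may be unevenly distributed, for example inadequate health literacy (an average SBSQ-D score of 2 or less). A facilitator could be reported with too narrow an interval, or a real barrier could be missed because its interval is too wide.

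**Working it through.** **1. The plan's own figure.** Users = uptake x sample. With the 500 per group in the Abstract ("random sample of 500 polypharmacy patients"), 0.10 x 500 = 50, which matches the target exactly. With the 550 per group in the sample-size section, 0.10 x 550 = 55. So the 10% appears to apply to the patients invited.

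**2. Adoption among those analysed.** The covariates come from the baseline questionnaire, so the regression runs on respondents. The stated participation is 25%-50%.
- Respondents per 500 invited: 0.25 x 500 = 125 to 0.50 x 500 = 250.
- If all 50 users respond, adoption is 50/250 = 20% to 50/125 = 40%. At the target of 50 users and 100 nonusers it is 50/150 = 33%.
- If the 10% applies to respondents instead, adoption is 10%, with 12.5-25 users per group (500 invited) or 13.75-27.5 (550 invited).

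The text does not settle which reading holds, so both are carried through.

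**3. Model SE against true SE.** Take one binary predictor with share q, adoption p1 where it is present and p0 where it is absent:
- Pooled residual variance: s2 = q p1(1-p1) + (1-q) p0(1-p0)
- Model variance of the risk difference: s2 / [q(1-q)] / n
- True variance: [p1(1-p1)/q + p0(1-p0)/(1-q)] / n

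The ratio does not depend on n, so a larger or pooled sample does not cure it. It equals 1 when q = 0.5, and also when p1 = p0.

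The prevalence q = 0.10 and the effects below are assumptions; the documents give neither.

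*Predictor raising adoption, 25% v 8%* (odds ratio (0.25/0.75)/(0.08/0.92) = 3.83):
- s2 = 0.1 x 0.1875 + 0.9 x 0.0736 = 0.0850
- Model: 0.0850/0.09 = 0.944
- True: 0.1875/0.1 + 0.0736/0.9 = 1.957
- SE ratio = sqrt(0.944/1.957) = 0.695; simulated coverage of the nominal 95% interval about 82%-83%

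*Predictor lowering adoption, 2% v 11%* (odds ratio 0.165):
- s2 = 0.1 x 0.0196 + 0.9 x 0.0979 = 0.0901
- Model: 0.0901/0.09 = 1.001
- True: 0.0196/0.1 + 0.0979/0.9 = 0.305
- SE ratio = sqrt(1.001/0.305) = 1.81; coverage above 99%

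**4. Range of adoption.** Each odds ratio and q = 0.10 are held fixed, and p0 is solved so that overall adoption takes the stated value (coverage simulated at n = 150 and 450):

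| Overall adoption | p1 v p0, OR 3.83 | SE ratio | Coverage | SE ratio, OR 0.165 |
|---|---|---|---|---|
| 10% | 25.7% v 8.3% | 0.698 | 83%-84% | 1.81 |
| 20% | 44.5% v 17.3% | 0.805 | 88%-89% | 1.70 |
| 33% | 62.3% v 30.1% | 0.957 | 94% | 1.52 |
| 40% | 69.0% v 36.8% | 1.034 | 96% | 1.42 |

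For the odds ratio of 0.165, coverage exceeds 99% in every row. With no association, coverage is about 95%-96% in every row.

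**5. Negative fitted probabilities.** Least squares was simulated on a 0/1 outcome with six covariates, one of them binary with 10% prevalence. The non-null odds ratios were assumed to be 1.2-2 in size (moderate) or 1.3-3 (strong).
- At 10% adoption: 5%-10% of fitted values fall below zero with moderate effects and 13%-16% with strong effects (n = 150-1500).
- At 33%: 1%-2% and 5%-6% (n = 150-450).

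**The case against.** The strongest case against is about size. The target of 50 users follows only if the 10% applies to those invited. Adoption in the regression sample would then be 20%-40%, and at 33% the too-narrow interval has nearly gone. This stands: a reader might take 10% as the prevalence in the model, but the documents do not establish it. Even so, the too-wide interval for a predictor that lowers adoption remains at about 1.5 times the true SE, and the 10% reading cannot be excluded.

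A reader might also infer that intervals are wrong for every uneven predictor, or that false positives are inflated. Neither is supported. The error needs both imbalance and a real association; in the single-predictor check the test of no association keeps its size. But real associations are what this analysis looks for.

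Negative fitted values matter less than the intervals, since the aim is to study effects and not to predict individual uptake. Whether effects are additive on the probability scale is unknown; only the unequal variance follows from the binary outcome.

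Finally, the Abstract also compares characteristics of users and nonusers by chi-square and t tests, barriers and facilitators are examined descriptively and qualitatively, and the study is declared exploratory. So the primary outcome does not rest on this model alone. None of this explains why a linear model was named for a yes/no outcome.

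**Conclusion.** The stated method does not fit the outcome defined in the same sentence, and that outcome comes first among the primary ones. This is a choice the article fixes, not a detail left to an analysis plan.

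The consequence is conditional. For an uneven predictor truly related to adoption, the SE can be about 30% too small (10% adoption, odds ratio about 3.8) or about 80% too large (2% v 11%). At the 50/100 target the same odds ratios give about 4% too small and about 50% too large. Balanced binary predictors and null effects are about right. These sizes rest on an assumed 10% prevalence, assumed odds ratios and a single-predictor calculation. That the model does not suit a binary outcome rests on none of these.

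A reader might go on to infer that patient group and practice must be added as covariates or that risk differences must be reported. The mismatch shown here does not require either.

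**What to change.** In the section on quantitative analysis at the patient level, replace multiple linear regression with multivariable logistic regression for adoption, and report odds ratios with 95% confidence intervals.

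Allow Firth penalisation as an option if adopters are few. With 12.5-27.5 users per group and at least six listed covariates, there could be as few as 12.5/6 = 2.1 to 27.5/6 = 4.6 users per covariate if groups are modelled separately.

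The cost is one sentence. The planned SPSS software supports logistic regression; whether the available version offers the Firth option should be checked. Sample, data collection and listed covariates need no change. The article says analysis is already underway, so the change should be made, and recorded as a change, before results are reported.

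### The adoption regression lists its covariates without patient group, the sampling stratum, so the age coefficient can absorb group differences in uptake if these follow the groups' age order

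*Protocol article*

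**What the plan says.** Under Outcomes of Interest, the protocol article puts this question first: "The primary outcomes of interest are the predictors for adoption of the PHR". Under Analysis of Quantitative Data at the Patient Level it states the method, "We will perform multiple linear regression analyses", and the covariates: the aim is to "investigate the effects of age, sex, education level, perceived health, health literacy, and internet and eHealth use on the adoption of the PHR". Adoption is a yes/no variable, "defined as having logged in at least once to the PHR and the summary record". Patient group is not on the list.

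In the same paragraph, the descriptive comparison of users and nonusers is by group, and so is the comparison of changes: "For each group of patients, we will compare the means changes in in-person levels". The regression sentence has no such qualifier.

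Under Setting, Study Population, and Sample Size, the reason for three samples is given: "Assuming that uptake, use, and effects will differ among different groups of patients, we will recruit a random sample from three groups of patients". Of polypharmacy patients and parents of young children it says: "They are likely to differ in terms of health status, age, internet use, and computer skills". Each group contributes a random sample of 550, with a target of 50 users and 100 nonusers.

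**The concern.** The article expects group to be related to the outcome of this model (uptake) and to several of its covariates (age, health status, internet use). A variable with both properties, left out of a regression, can shift the coefficients of the covariates it is related to. Age is the most exposed, because parents of children under 4 are mostly young adults and polypharmacy patients are mostly older.

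At stake is the reading of a primary outcome. An age coefficient could be reported as a predictor of adoption when it partly reflects membership of the polypharmacy or parent sample. Its size would also depend on the equal sampling of the three groups, since no weighting to the practice population is described. Presence of a chronic disease, which Table 1 lists as a determinant of uptake, is not among the regression covariates either, so it cannot stand in for the polypharmacy group.

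**Working it through.** **1. Inputs from the article.** Covariates: age, sex, education, perceived health, health literacy, internet and eHealth use. Test level: two-sided 0.05. Target per group: 50 users + 100 nonusers = 150, so an average user share of 50/150 = 33%. The 50 users are consistent with 10% uptake among 500 invited: 500 × 0.10 = 50. The sample of 550 shrinks to 500 if GPs exclude 1 − 500/550 = 9%.

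**2. Inputs that are assumed.** The article gives no uptake, age or health distribution by group. Two sets of assumptions were used, in the order parents / others / polypharmacy:
- Set A: mean age 32/46/63 (SD 5/15/8, limited to 18–75), perceived health lower in the polypharmacy group, other covariates unrelated to group.
- Set B: mean age 33/48/63 (SD 5/15/9, same limits), perceived health 3.7/3.3/2.5 (SD 0.9), internet score 4.3/3.8/3.0 (SD 0.8).

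In both, adoption depends on group only, so there is no age, health or internet effect within any group.

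**3. The mechanism by hand (set B, age as the only covariate, no age limits).** With equal group sizes, the pooled age slope is the between-group covariance of age and uptake divided by the total variance of age.
- Uptake 43/34/23%, mean 33.3%. Covariance = [(−15)(0.0967) + 0 + (15)(−0.1033)]/3 = −1.0.
- Variance of age: between groups (225 + 0 + 225)/3 = 150; within groups (25 + 225 + 81)/3 = 110.3; total 260.3.
- Slope = −1.0/260.3 = −0.0038 per year, or about −3.8 percentage points per decade, with no age effect in any group.
- Standard error ≈ √(0.333 × 0.667)/√(450 × 260.3) = 0.471/342.3 = 0.00138, so z ≈ −2.8.
- Uptake 40/20/40%: covariance = [(−15)(0.0667) + 0 + (15)(0.0667)]/3 = 0, so the slope is 0.

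The second case shows that a group difference alone is not enough; it must run along age.

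**4. Full model by simulation, 150 per group.** Share of trials in which the age test rejects:

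| Uptake, parents/others/polypharmacy | Assumptions | Without group | With group |
|---|---|---|---|
| 33/33/33% | B | 5% | 6% |
| 28/33/38% | A | 24% | 5% |
| 38/34/28% | B | 15% | 5% |
| 23/33/43% | A | 72% | 5% |
| 43/34/23% | B | 48% | 5% |
| 33/24/43% | B | 11% | 4% |
| 40/20/40% | B | 5% | 4% |

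A separate simulation of 28/33/38% and 23/33/43% gave 26% and 75% without group, and 18% and 56% once internet use was also allowed to differ by group, as the article expects. Part of the group difference then loads on internet use instead of age.

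**5. Other covariates.** Without group, the perceived-health test rejects in 6% to 15% of trials across the set A scenarios (these include larger gaps and samples), and in 6% to 11% in set B at 150 per group. Internet use in set B reaches 13% at 43/34/23%. With group included, both return to about 5%.

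**6. Lower uptake, larger samples.** At 550 × 0.375 = 206 per group (set A), uptake 7/10/13% gives 30% for age and 5/10/15% gives 65%. At 500 per group (set B), 12/10/8% gives 19% and 15/10/5% gives 79%. With group, all are 5% to 6%.

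**The case against.** The strongest reply is that a pooled fit is inferred, not stated. The article says analyses in the plural, draws three separate samples, and runs the neighbouring analyses by group; a fit within each group would remove the problem. This stands as a limit. Pooled is the more natural reading, because the qualifier appears before and after this sentence but not in it, but it is not certain.

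A reader might infer that the plan itself expects a biased age test. The article does not support that. It says uptake differs among groups, not that it rises or falls with age. It also describes both polypharmacy patients and parents as frequent users of GP services, which would fit a high/low/high pattern across age, and in that pattern the age test is hardly affected. Nor does the article support a claim that perceived health would be seriously distorted, or that group uptake would stay hidden: the descriptive analysis by group would show it.

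It can also be said that age and health may be the reason the groups differ, so an unadjusted coefficient is a legitimate overall association. That is fair for an exploratory study, and the simulated null of no effect within any group is a chosen one. But the overall association from three equal samples, unweighted, is not that of the practice population unless the groups happen to be equally large, and the listed model cannot separate within-group from between-group contributions.

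**Conclusion.** The point holds in conditional form. As listed, and on its natural pooled reading, the model for a primary outcome omits the variable the study samples by, although the article expects that variable to be related to uptake and to several covariates. If uptake follows the age order of the groups, the age coefficient can carry the group difference: roughly 15% to 75% rejection with no within-group age effect, for gaps of 10 to 20 points at 150 per group, against about 5% with group included. If uptake is not ordered by age, the inflation is small (about 11% at 33/24/43%) or absent (40/20/40%). Perceived health is affected much less. These sizes rest on assumed ages, health scores, internet scores and uptake by group, none of which the article gives. The use of linear regression for a yes/no outcome is a separate matter and plays no part here.

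**What to change.** In Analysis of Quantitative Data at the Patient Level, add patient group (three levels) to the covariates of the adoption model and report its coefficients. The age, health and internet-use coefficients are then within-group effects, and the assumed difference in uptake between groups is itself estimated. If separate models per group were intended, say so; with a target of only 50 users per group, one model with group terms is the more economical choice.

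The cost is one sentence and two parameters. Group is known for every participant from the sampling. The intervals for age and perceived health become somewhat wider, because part of their variation lies between the groups.
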